### **Subject management following completion of study**

Following completion, if the study assessment identifies a remaining unmet treatment need, subjects will be encouraged to seek such treatment within or without the current clinic. Referrals to other treatment providers will be offered, should they be deemed adequate.

### **Stopping rules and interim analyses**

The trial will be terminated if serious adverse events are encountered that prompt a re-evaluation of the risks involved, or if accrual indicates that it will not complete within a reasonable timeframe. No interim analyses are planned.

### **Compensation**

Subjects will receive a gift certificate of 50 SEK (approximately 7 USD) after sessions 1-11 of COPE and at the completion of session 12 and the CAPS immediately thereafter. Subjects will then receive gift certificates of 150 SEK (approximately 20 USD) at follow ups six and nine months post baseline.

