**Sessions 6 (+ 0-7 days) and 12 (+ 0-7 days)**

CAPS-5  
CGI

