### **Randomization**

Karolinska Trial Alliance (KTA) will be responsible for the randomization, which will be insulated from the researchers. Subjects will be randomized in blocks, 1:1 to receive relapse prevention or COPE. When subjects are included the PI or coordinator at The Stockholm Centre for Dependency Disorders is to be contacted and to provide both the subject with the appropriate randomization number and information on whether the subject is to receive relapse prevention or COPE, information which is kept in a sealed envelope for each randomization number until inclusion, when the applicable envelope is opened and the site is informed of what treatment to give the subject.

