### **Treatment**

COPE (12, 13, 35) will be delivered by trained therapists, and consists of twelve individual 90-minute sessions. Its key elements include repeated imaginal exposure (i.e. revisiting and recounting traumatic memories) and processing of traumatic memory (i.e. discussing thoughts and feelings related to revisiting the memory and cognitive restructuring). Participant homework includes repeated listening to a recording of the recounting made during the last session, and repeated *in vivo* exposure to safe situations previously avoided because of trauma related distress. If participants demonstrate no or minimal distress when recounting the traumatic memory and confronting situations previously avoided because of trauma related anxiety, any remaining sessions will focus on other psychosocial problems.

All COPE sessions will be digitally recorded, transferred to a computer, encrypted and stored on a remote file sharing service. They will be viewed by supervisors, e.g. licensed psychologists and psychotherapists, supervising the therapists and providing feedback on their delivery of COPE. Sessions may also be viewed in supervision.

The relapse prevention, a Swedish version of the Project MATCH Cognitive Behavioral Coping Skills Therapy Manual (36), will be delivered by trained therapists. It consists of twelve 45-60-minute sessions, and includes skills such as becoming aware of and dealing with craving. COPE

and RP sessions will be digitally recorded and 10-15 percent of sessions will be monitored for fidelity.

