***Follow up - at each session, after session 6 and 12 and six and nine months post baseline***

Prior to each COPE or RP session, each subject will fill out self-assessment forms on PTSD-symptom severity (PCL-C), alcohol consumption (TLFB), alcohol craving (PACS), anxiety symptom severity (STAI) and depression symptom severity (BDI-II). For information on follow ups at sessions 6 and 12 and six and nine months post baseline, see summary above on pages 8-10.

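### As written, the 50 SEK session certificates for sessions 1-11 name COPE only; if applied that way, one arm has an attendance incentive at visits that supply TLFB and PCL-C data

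*Combined protocol and SAP*

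**What the plan says.** The Compensation section has three parts.

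- Sessions 1-11: "Subjects will receive a gift certificate of 50 SEK (approximately 7 USD) after sessions 1-11 of COPE". RP is not mentioned.
- The end of treatment: "and at the completion of session 12 and the CAPS immediately thereafter". The arm is not restated, and it is not clear whether this is one certificate or two.
- Follow-up: "Subjects will then receive gift certificates of 150 SEK (approximately 20 USD) at follow ups six and nine months post baseline". No arm is named, so this covers everyone.

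Allocation is equal: "Subjects will be randomized in blocks, 1:1 to receive relapse prevention or COPE". Both therapies have the same number of sessions. Under Treatment, COPE "consists of twelve individual 90-minute sessions", and of RP the protocol says "It consists of twelve 45-60-minute sessions".

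Outcome data are collected at those sessions in both arms: "Prior to each COPE or RP session, each subject will fill out self-assessment forms". The forms include TLFB and PCL-C. The SAP takes baseline, sessions 1-12 and the two follow-ups into the co-primary alcohol model (Alcohol use) and into the PCL-C model (Self-rated PTSD symptom severity). CAPS-5 and the PEth blood samples are scheduled at sessions 6 and 12 and at the two follow-ups.

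**The concern.** A payment for attending sessions, made in one randomised arm only, is a co-intervention. Here the session is both the unit of treatment and the occasion for data collection. If the payment changes attendance, it changes the therapy received and the number of TLFB and PCL-C records supplied, in one arm and not the other. Differences in retention, and to some extent in session-level outcomes, could then partly reflect the incentive.

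Two features of the plan add to the exposure. The Subjects section replaces participants who lack complete outcome data, so completion that differs by arm could influence who counts among the 120 completers. The SAP specifies one model per outcome and no sensitivity analysis for missing data.

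**Working it through.** The plan gives no figure for the effect of the payments, so there is none to reproduce. The check adds up the payments by arm and counts the time points they touch.

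**Inputs.** 50 SEK (about 7 USD) per certificate and 150 SEK at each of two follow-ups (Compensation); twelve sessions in each arm (Treatment); 1:1 allocation (Randomization); a maximum of 150 participants (Subjects); time points from the SAP.

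**1. Payments stated for one arm or for all.**
- Sessions 1-11, COPE named: 11 x 50 = 550 SEK, or 11 x 7 = about 77 USD.
- Session 12 and the CAPS after it, arm unclear: 50 SEK if one certificate, 2 x 50 = 100 SEK if two.
- Follow-up, everyone: 2 x 150 = 300 SEK.

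**2. Totals by arm under each reading of the session-12/CAPS certificate.**

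| Reading | COPE (SEK) | RP (SEK) | Gap (SEK) |
|---|---|---|---|
| One certificate, COPE only | 550 + 50 + 300 = 900 | 300 | 600 |
| Two certificates, COPE only | 550 + 100 + 300 = 950 | 300 | 650 |
| One certificate, both arms | 900 | 50 + 300 = 350 | 550 |
| Two certificates, both arms | 950 | 100 + 300 = 400 | 550 |

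The gap is 550 to 650 SEK. On every reading it exceeds what an RP participant can receive in total (300 to 400 SEK). If the session certificates covered both arms, each arm could receive 900 or 950 SEK and the gap would be 0.

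**3. Time points affected.** TLFB and PCL-C: 1 baseline + 12 sessions + 2 follow-ups = 15. The unequal payment touches sessions 1-11, 11/15 = 73%, or sessions 1-12, 12/15 = 80%, if the session-12 certificate is for COPE only.

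**4. CAPS-5 and PEth.** Each has four post-baseline time points. Session 6 falls in the COPE-only range, session 12 is unclear, and the six- and nine-month points are paid equally. The follow-up CAPS is done by telephone no later than seven days after the session or follow-up visit (Blind assessors), so its link to attendance is looser than for forms completed at the session.

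**5. Effect on the estimates.** This cannot be calculated. The documents give no attrition by arm, no effect size, no standard deviation and no relation between payment and attendance.

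**The case against.** The strongest objection is that the wording is a slip. The grammatical subject of the sentence is all subjects, and the next sentence continues with the same group and plainly covers both arms. The protocol names COPE alone elsewhere when it must mean more: Study start times the stopping of AUD medication relative to COPE for people not yet randomised, and Treatment first says that COPE sessions are recorded and later that both are. Against this, the protocol names both therapies where it describes the session forms, the blinded assessments and the fidelity recordings. The documents do not settle the question. The consent pages, which might describe payment, were not available. The slip reading therefore stands as a real possibility.

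A reader might also infer that RP participants are unpaid at every outcome visit. They are not: the six- and nine-month payments are equal, and the session-12/CAPS certificate may be shared.

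A reader might go further and conclude that no COPE benefit could be separated from the incentive, or that missing data necessarily become arm-dependent. The documents do not support either. The payment is about 7 USD per session, for attendance and not for abstinence or symptom change. The SAP's intention-to-treat mixed models include all randomised participants, and missingness that differs by arm does not bias such a model by itself if it depends only on observed data. What remains is that the model cannot correct for missingness that depends on unobserved drinking or symptoms, and cannot remove an effect of the incentive on the amount of therapy received.

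Finally, COPE sessions are longer (90 against 45-60 minutes). The payment might offset a greater burden rather than create an imbalance, so the direction is unknown. The Compensation section does not give this as a reason, and it would not by itself explain the absence of any session payment for RP.

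**Conclusion.** The point holds conditionally. On its literal wording the protocol gives COPE participants 550 to 650 SEK that RP participants do not receive, over 11 or 12 of the 15 TLFB and PCL-C time points. If sites paid by that wording, differential attendance and data completeness are plausible in the session-level data, and less so in the session 6 and 12 measures. The equally paid follow-ups are not directly affected.

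This rests on two things the documents leave open: whether the naming of COPE alone was intended, and which arm the session-12/CAPS certificate covers. It does not establish that the arms were in fact paid differently, or that any result is biased. It is worth resolving because the correction is cheap and session data feed a co-primary outcome.

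**What to change.** Reword the Compensation sentence so that the certificates for sessions 1-11 apply to COPE or RP. State that the session-12/CAPS payment applies in both arms, and whether it is one certificate or two.

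The cost is modest. Assuming 150/2 = 75 per arm and full attendance, it is 75 x 550 = 41,250 SEK if RP already receives the session-12/CAPS payment. Otherwise it is 75 x 600 = 45,000 SEK with one such certificate, or 75 x 650 = 48,750 SEK with two, plus a short amendment.

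The rewording may come too late. The SAP is dated 241022 and already refers to two participants without current PTSD at baseline, so enrolment has begun. If treatment is complete:

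- Check the payment records and state what each arm received. If the arms were paid alike, correct the text and the matter is closed.
- If they were paid differently, tabulate sessions attended and missing TLFB, PCL-C, CAPS-5 and PEth data by arm and time point.
- In that case also report the unequal incentive as a limitation, and do not present a retention difference as a treatment effect.

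This needs no new data from participants, only the payment records and a descriptive table.

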### **Information to participating staff**

Participating staff will be required to read the protocol and key background literature, and document having done so. They will discuss these materials at a joint site-initiation meeting with the Principal Investigator and co-investigators, and their participation will be documented.

Staff will have quarterly meetings, and will have ongoing interactions with the Principal Investigator and co-investigator over the course of the study.

### **Delegation policy**

All sponsor responsibilities with the exception of subject withdrawal decisions, adverse event reporting and study termination decisions will be delegated to a lead investigator at each of the participating sites.

### **Publication policy**

Results will be submitted for publication in a peer-reviewed journal.

## COPE vs RP RCT statistical analysis plan 241022

One pre-selected model per outcome will be run. There will be no testing for differences at baseline.

### Co-primary outcomes

#### Clinician-rated PTSD symptom severity

Difference in PTSD symptom severity, measured using CAPS-5, between groups up to 9-month follow-up. To be analyzed using a linear mixed model (LMM) with fixed effects for treatment, time and their interaction, a random effect for subjects and a random intercept. Restricted maximum likelihood estimation, Satterthwaite approximation, and a first-order autoregressive covariance matrix are to be used.

Data from baseline, mid-treatment (session 6) and the last treatment session (session 12), 6- and 9-month follow-ups when CAPS-5 was conducted.

Intention-to-treat (ITT) analysis will include all randomized participants, results will be presented. A modified ITT analysis will be run without the two participants who did not have current PTSD at baseline, results will be presented.

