**Study population:** Up to one hundred and fifty treatment-seeking women, aged >18, diagnosed with DSM-5 PTSD and moderate to severe AUD.

**Method:** The study consists of three consecutive phases for each patient: *A screening and randomization phase*, carried out over the course of three to four visits, including diagnostic assessment and randomization 1:1 to receive COPE or RP, *a phase with cognitive and*

*behavioral therapy*, 12 sessions of COPE or 12 sessions of RP, typically one a week, and *a posttreatment follow up*, at session 12, and six and nine months post baseline.

**Outcomes:** The co-primary outcomes will be 1) change from baseline in PTSD symptom severity (Clinician-Administered PTSD Scale (CAPS-5)), measured after sessions 6 and 12 and six and nine months post baseline. 2) change from baseline in alcohol consumption per week (grams per week) and heavy drinking days (HDD) derived from Timeline Follow Back (TLFB), after therapy sessions 6 and 12 and six and nine months post baseline.

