## **Summary of study procedures and assessments**

### ***Recruitment and screening***

Subjects will be recruited among treatment seeking women at the outpatient units at Capio Maria in Stockholm, the Stockholm Centre for Dependency Disorders and Linköping University Hospital, all in Sweden. Information about the study may be posted within the Stockholm County health care system, and on the web pages of Capio Maria, The Stockholm Centre for Dependency Disorders and Linköping University Hospital. Women seeking treatment for problems related to alcohol use or PTSD will be assessed for eligibility. Once informed consent is obtained baseline measures will be gathered during a series of screening visits, as detailed in Appendix 1.

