#### Alcohol use

Difference in grams of alcohol consumed per week, measured using Timeline Follow Back (TLFB), between groups up to 9-month follow-up. To be analyzed using an LMM with fixed effects for treatment, time and their interaction, a random effect for subjects and a random intercept. Restricted maximum likelihood estimation, Satterthwaite approximation, and a first-order autoregressive covariance matrix are to be used.

Data from baseline, sessions 1-12, 6- and 9-month follow-ups when TLFB was completed.

ITT and modified ITT as above.

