### A biomarker of alcohol use

A biomarker of alcohol use (PEth) in blood. To be analyzed using an LMM with fixed effects for treatment, time and their interaction, a random effect for subjects and a random intercept. Restricted maximum likelihood estimation, Satterthwaite approximation, and a first-order autoregressive covariance matrix are to be used.

Data from baseline, mid-treatment (session 6) and the last treatment session (session 12), 6- and 9-month follow-ups when blood samples were taken.

ITT and modified ITT as above.

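### The mixed models give each randomised arm its own baseline mean; a common baseline mean, paired with visit-specific variances, would estimate the same effect more precisely

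*Combined protocol and SAP*

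**What the plan says.** In the SAP, the section on clinician-rated PTSD symptom severity specifies a "linear mixed model (LMM) with fixed effects for treatment, time and their interaction, a random effect for subjects and a random intercept". The rows analysed are "Data from baseline, mid-treatment (session 6) and the last treatment session (session 12), 6- and 9-month follow-ups when CAPS-5 was conducted", so baseline is one of five modelled occasions. There is no baseline covariate and no constraint on the baseline means. On estimation: "Restricted maximum likelihood estimation, Satterthwaite approximation, and a first-order autoregressive covariance matrix are to be used".

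The alcohol section repeats the structure ("To be analyzed using an LMM with fixed effects for treatment, time and their interaction") over baseline, sessions 1-12 and two follow-ups, which makes 15 occasions. PCL-C follows the same schedule. PEth has the five-occasion schedule: "Data from baseline, mid-treatment (session 6) and the last treatment session (session 12), 6- and 9-month follow-ups when blood samples were taken".

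The protocol Summary defines the PTSD co-primary as "change from baseline in PTSD symptom severity". Under Randomization: "Subjects will be randomized in blocks, 1:1 to receive relapse prevention or COPE". Under Recruitment and screening, "baseline measures will be gathered during a series of screening visits", and the study overview lists randomisation after the week 0 assessments.

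The SAP opens by allowing one pre-selected model per outcome and ruling out tests of baseline differences. It does not say whether time is categorical or continuous, or which contrast is the primary test.

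**The concern.** Baseline is measured before randomisation, so the two arms have the same expected baseline mean. The SAP model nevertheless estimates a separate baseline mean in each arm and subtracts it in full. Each change contrast then carries the whole chance difference at baseline, including measurement noise. The contrast remains unbiased, but its standard error is larger than it need be.

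Precision on both co-primary outcomes is at stake. Recruitment is capped at 150, and with one model per outcome there is no baseline-adjusted analysis beside the main one. The information needed is already in the data set.

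**Working it through.** **Inputs.** From the documents: 1:1 allocation, at most 150 recruited for 120 completers (60 per arm), five CAPS-5 occasions, random intercept plus AR(1). The documents give no SD, correlation, effect size or power, so there is no figure of the plan's own to reproduce. The correlation r and the SDs below are assumptions, shown as ranges.

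**Step 1: what the SAP model estimates.** With categorical time and complete data, the treatment-by-time estimate should equal the difference in mean raw change. In a generated data set it did so at every visit (at 9 months, -0.2932 by both methods). With dropout it becomes a likelihood-based difference in change; with linear time it becomes a difference in slopes.

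**Step 2: same estimand.** In 4,000 simulated trials with a true effect of -0.50 and 60 per arm, the mean estimate was -0.500 for the SAP model and -0.502 with a common baseline mean. The empirical SEs were 0.197 and 0.165, a ratio of 0.837; theory gives 0.838.

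**Step 3: gain with equal SDs.** Per arm and per patient, the variance is proportional to

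- SAP model: 2s²(1-r)
- common baseline: s²(1-r²)

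The ratio is (1+r)/2, so the reduction is (1-r)/2.

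| r | Variance reduction | SE ratio at 9 months, complete data, 60 per arm | SE ratio, 75 per arm, 20% dropout |
|---|---|---|---|
| 0.3 | 35% | 0.81 | 0.83 |
| 0.5 | 25% | 0.87 | 0.89 |
| 0.7 | 15% | 0.92 | 0.93 |

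At r = 0.5 with complete data, 150 patients carry the information of 150/0.75 = 200. A contrast with 80% power under the SAP model would have about 94%, 90% and 86% in the three rows (complete data). If time is linear, the SE ratio was 0.74-0.95 over r of 0.1-0.7.

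**Step 4: unequal SDs, correct covariance.** With baseline SD s0 and follow-up SD s1, the proportional variance gain is

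(s0 - r·s1)² / (s0² + s1² - 2r·s0·s1).

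For s0 = 0.75 and s1 = 1.1:

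- r = 0.3: 0.1764/1.2775 = 14%
- r = 0.5: 0.0400/0.9475 = 4%
- r = 0.7: 0.0004/0.6175 = 0.06%

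The gain is zero at r = 0.75/1.1 = 0.68. The numerator is a square, so with a correct covariance there is no large-sample loss.

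**Step 5: unequal SDs, SAP covariance kept.** A random intercept plus AR(1) imposes one variance on all visits. With two visits and SD ratio q = s1/s0, the fitted correlation tends to w = 2qr/(1+q²), and the squared ratio of true SEs is

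(q² + w² - 2wrq) / (q² + 1 - 2rq).

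For q = 1.1/0.75 = 1.467 and r = 0.7: w = 0.652, and the squared ratio is 1.238/1.098, so the SE ratio is 1.06. This is a loss. The printed SE would still appear to fall, by the factor √((1+0.652)/2) = 0.91.

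For the five-visit design, the large-sample fit of the SAP structure with true (sandwich) SEs gives, at 9 months:

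| r (approx.) | SE ratio, equal SDs | SE ratio, SD rising from 0.75 to 1.1 |
|---|---|---|
| 0.34 | 0.82 | 0.95 |
| 0.53 | 0.88 | 1.01 |
| 0.72 | 0.93 | about 1.07 |
| 0.81 | not tabulated | 1.09 |

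The direction of the effect therefore depends on whether the covariance structure is relaxed together with the mean structure.

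**The case against.** The strongest reply is that the plan contains no error. The model is unbiased, it matches the protocol's change-from-baseline wording, and chance imbalance is already reflected in the SE of a change contrast. All of that stands, and it limits the point to efficiency.

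A second reply also stands. Changing only the mean structure is not safe under the SAP's covariance, as Step 5 shows, and unequal SDs are plausible here. Entry requires current PTSD, which can narrow the baseline CAPS-5 distribution. Baseline TLFB covers 90 days, whereas TLFB is also completed before each session, so the values may differ in spread. The equal-SD figures are therefore one end of a range, and a reader might wrongly infer that the constraint can never do harm.

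A further inference to resist is that the SAP tests a treatment main effect averaged over all occasions, so that the pre-treatment row dilutes the result. The SAP names no contrast, but it specifies the interaction, and the protocol's outcome is change from baseline. Nothing in the documents says that an averaged main effect is the test.

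On cost, the SAP is dated 241022 and already refers to two participants without current PTSD at baseline, so some baseline data had been seen. The documents do not show that outcomes by arm had been seen. This argues for documenting the change and its timing, not for leaving the models as they are.

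**Conclusion.** The point holds as an efficiency improvement. It is not a finding of bias or invalidity, and the documents support no such reading.

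- **Equal SDs, complete data:** 15-35% less variance for r of 0.7-0.3 (SE 8-19% smaller), and somewhat less with dropout.
- **SD rising from 0.75 to 1.1, covariance relaxed:** about 0-14% less variance over the same r.
- **The same SDs, SAP covariance kept:** little gain at low r, and a true SE up to about 7-9% larger at r of 0.7-0.8.

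These figures rest on assumed correlations and SDs, on randomisation making the expected baseline means equal, and, for the exact formulas, on categorical time. The constraint also remains valid in the modified ITT set, because the two exclusions are made on a baseline characteristic. The choice of primary time point is a separate gap that this change does not fill.

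**What to change.** In the CAPS-5, alcohol, PCL-C and PEth models:

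- Use categorical time plus treatment-by-time terms for the post-baseline occasions only, with no treatment effect at baseline.
- Keep the baseline rows, so that everyone randomised with a baseline value contributes.
- Replace the equal-variance random intercept plus AR(1) with a covariance that lets variances differ by visit: unstructured for the five-occasion outcomes (CAPS-5, PEth), and heterogeneous AR(1) or similar for the 15-occasion outcomes (alcohol, PCL-C).

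The cost is a short SAP edit, a small change of code and a few more covariance parameters. No new data are needed and no participants are lost. Removing the baseline treatment term also fits the SAP's decision not to test for baseline differences. Document the change before outcomes by arm are seen; if they have already been seen, report it as a labelled sensitivity analysis beside the planned model.

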***Treatment (week 1-12, to be completed over a maximum of 20 weeks)***

*Assessments*

PTSD-symptom severity (PCL-C)  
Anxiety symptom severity (STAI)  
Depression symptom severity (BDI-II)  
Alcohol consumption (TLFB)  
Alcohol craving (PACS)

*Biological samples*

Urine screening for alcohol and illicit drugs (U-Etg etc.)

*Treatment*

COPE or RP (Project MATCH 12 sessions)

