***Follow up six and nine months post baseline (approximately weeks 26 and 38)***

*Interview and assessments*

PTSD diagnosis and symptom severity (CAPS-5, PCL-C)

Anxiety symptom severity (STAI)

Depression symptom severity (BDI-II)

Alcohol consumption during the past 90 days (TLFB)

Alcohol craving (PACS)

Alcohol dependence severity (ADS, AUDIT)

Level of function in important areas of life (ASI-SR)

Clinical Global Impression (CGI)

Intelligence (Matrigma)

Personality (NEO-FFI-3)

Health care consumption (TIC-P)

Treatment credibility/expectancy (The Credibility/Expectancy Questionnaire)

Working alliance (WAI-S)

*Biological samples*

Blood samples: complete blood count (Hb, MCV, TPK, LPK), liver function tests (ASAT, ALAT, GGT), alcohol marker (PEth)

Cortisol in hair

Urine screening for alcohol and illicit drugs (U-Etg etc.)

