## Secondary outcomes

### Self-rated PTSD symptom severity

Measured using the PTSD Checklist – Civilian version (PCL-C), range 17-85. To be analyzed using an LMM with fixed effects for treatment, time and their interaction, a random effect for subjects and a random intercept. Restricted maximum likelihood estimation, Satterthwaite approximation, and a first-order autoregressive covariance matrix are to be used.

Data from baseline, sessions 1-12, 6- and 9-month follow-ups when PCL-C was completed.

ITT and modified ITT as above.

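### For weekly alcohol grams and PCL-C, an autoregressive covariance by visit order treats 1-week and 14-week gaps alike, so the treatment-by-time test can run at about 7–13% instead of 5%

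*Combined protocol and SAP*

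**What the plan says.** The SAP gives the same model for CAPS-5, alcohol, PCL-C and PEth: fixed effects for treatment, time and their interaction, "a random effect for subjects and a random intercept", which I read as one subject-level random intercept, and then "Restricted maximum likelihood estimation, Satterthwaite approximation, and a first-order autoregressive covariance matrix are to be used".

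The occasions differ by outcome:

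- **Alcohol (co-primary):** "Data from baseline, sessions 1-12, 6- and 9-month follow-ups when TLFB was completed".
- **PCL-C (secondary):** "Data from baseline, sessions 1-12, 6- and 9-month follow-ups when PCL-C was completed".
- **CAPS-5 (co-primary):** "Data from baseline, mid-treatment (session 6) and the last treatment session (session 12), 6- and 9-month follow-ups when CAPS-5 was conducted". PEth follows the same five visits.

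On timing, the protocol Summary describes "12 sessions of COPE or 12 sessions of RP, typically one a week". The overview in Study design and methods has "Treatment (week 1-12, to be completed over a maximum of 20 weeks") and follow-up at "six and nine months post baseline (approximately weeks 26 and 38").

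The opening lines of the SAP allow one pre-selected model per outcome. The SAP does not state the time metric of the autoregressive term, whether time is categorical or continuous, or whether the variance may change between visits. It names no robust standard error, alternative covariance or fallback.

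**The concern.** A standard first-order autoregressive matrix has one correlation per step and one variance. If steps are visits, two sessions a week apart are assumed to be as closely correlated as session 12 and the 6-month visit, which are nominally 14 weeks apart. The fitted values have to compromise. With fifteen occasions, thirteen of them inside the first 12 weeks, the compromise is set mainly by the weekly sessions.

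With categorical time and complete data, the estimated arm differences do not depend on the covariance, but their standard errors and the interaction test do. What is at stake is therefore the type I error and interval coverage of a co-primary outcome, with no second analysis planned that would reveal a problem.

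**Working it through.** **Inputs from the documents.** Nominal weeks are 0, 1 to 12, 26 and 38 for alcohol and PCL-C, and 0, 6, 12, 26 and 38 for CAPS-5 and PEth.

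- 15 occasions: twelve gaps of about 1 week, then 26 − 12 = 14 and 38 − 26 = 12.
- 5 visits: gaps of 6, 6, 14 and 12. If treatment takes the full 20 weeks, evenly spread: 10, 10, 6 and 12.

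**No plan figure to reproduce.** The documents state no SD, within-subject correlation, standard error or alpha. The 5% level and everything below on variances are assumptions, shown as ranges.

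**Assumed truth.** Total variance 1: intercept share r (0.1 to 0.5), noise (nugget) share n (0 or 0.1), and the remainder decaying with half-life h (4 to 20 weeks). The covariance at a gap of d weeks is r + (1 − r − n)·0.5^(d/h).

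**Working model.** Random intercept a plus AR(1) by visit order with variance b and correlation ρ, at the values closest to the truth in the Kullback–Leibler sense (the large-sample fit). Time is categorical.

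**Formulas.** For change from baseline at a visit d weeks and k steps later, the intercept and the sample-size factor cancel in the ratio:

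- true variance ∝ 2[1 − r − (1 − r − n)·0.5^(d/h)]
- model variance ∝ 2b(1 − ρ^k)
- SE ratio = √(model/true)
- two-sided error = 2Φ(−1.96 × ratio)

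**Example 1, no noise** (r = 0.5, h = 6, n = 0). The fit is a = 0.565, b = 0.425, ρ = 0.758.

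- Session 1: true 2 × 0.5 × (1 − 0.891) = 0.109; model 2 × 0.425 × (1 − 0.758) = 0.206. Ratio √(0.206/0.109) = 1.37, error 0.007.
- 9 months (d = 38, k = 14): true 1 × (1 − 0.012) = 0.988; model 0.850 × (1 − 0.021) = 0.832. Ratio 0.918, error 0.072.
- Joint 14-df interaction test: about 0.11.

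**Example 2, with noise** (r = 0.2, n = 0.1, serial correlation 0.7 at 6 weeks). The fit is a = 0.533, b = 0.450, ρ = 0.574. The weekly sessions push the intercept share from 0.2 to about 0.53, so the model overstates the link between baseline and 9 months.

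- 9 months: true 2 × (0.8 − 0.7 × 0.1045) = 1.454; model 0.900 × (1 − 0.0004) = 0.900. Ratio 0.787, error 0.123. Joint error about 0.08.

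**Over the whole grid, constant variance, weekly sessions** (model SE / true SE):

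| | Session 1 | Session 6 | Session 12 | 6 months | 9 months | Joint error |
|---|---|---|---|---|---|---|
| 15 occasions, no noise | 1.29–1.54 | 1.10–1.45 | 1.00–1.37 | 0.94–1.06 | 0.92–0.97 | 0.096–0.128 |
| 15 occasions, 10% noise | 1.09–1.19 | 1.05–1.21 | 0.94–1.01 | 0.81–0.91 | 0.74–0.91 | 0.067–0.081 |
| 5 visits, no noise | – | 1.09–1.21 | 1.04–1.18 | 1.00–1.02 | 1.00 | 0.051–0.056 |

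The 0.97 at 9 months comes from one corner (r = 0.1, h = 20); elsewhere the row is 0.92 to 0.96.

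**Unequal variances, CAPS-5, weekly schedule.** If the SD rises from 1.0 to 1.5 after baseline, the ratios run 1.01–1.38. If it falls from 1.0 to 0.6, they run 0.85–0.97.

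**Does indexing by weeks repair it?** For 15 occasions with constant variance, the joint error falls from 0.075–0.109 to 0.049–0.062 over a set of scenarios with r from 0 to 0.5, 6-week serial correlation 0.5 to 0.8 and n of 0 or 0.1. Without noise the ratios become exactly 1.00. With noise but no noise term in the model, Example 2 still gives 0.867 at 9 months, so that term is needed. Week-indexing does not cure unequal variances: CAPS-5 ratios remain 1.02–1.16 if the SD rises and 0.81–0.89 if it falls.

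**The case against.** **The time metric is inferred.** The SAP names no metric, and a week-based structure may be intended. That stands: visit order is the ordinary meaning of the term, not a stated choice. If weeks are meant, the SAP has to say so.

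**The true covariance is unknown.** That also stands. The percentages depend on the assumed grid, and the larger 9-month shortfall needs measurement noise. If the alcohol SD falls after baseline, the joint error is about 6–8%. If treatment is spread evenly over 20 weeks, the fifteen occasions have gaps of 20/12 ≈ 1.7 weeks, then 6 and 12, and the same calculation gives a joint error of about 6–9%. The problem shrinks but keeps its direction.

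**Stronger readings the documents do not support.** A reader might infer that the CAPS-5 standard errors are wrong in both directions because gaps run from 1 to 14 weeks. CAPS-5 has no 1-week gaps. Spacing alone makes its session 6 and 12 standard errors up to about 20% too large, leaves 6 and 9 months about right, and the inflation disappears on the 20-week schedule. A reader might also argue that diagnosis at entry narrows the baseline spread, so the SD must rise. Entry is by MINI and clinical examination without a CAPS-5 cut-off, and the ITT set keeps two participants without current PTSD, so either direction is possible. Nor is bias from dropout a reason to act: in simulation with an assumed 24% outcome-dependent dropout in one arm it was at most about 0.03 SD.

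**The SAP was written with some data known.** It already refers to those two participants. Replacing a pre-selected model therefore needs documentation, which shapes the fix.

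**Conclusion.** The point holds for the alcohol co-primary and PCL-C. Under week-based decay with constant variance and roughly weekly sessions, a nominal 5% joint treatment-by-time test runs at about 7–13%. First-session standard errors are about 10–50% too large. The 9-month standard error is about 4–8% too small without measurement noise and up to about 26% too small with 10% noise. If time were instead fitted as a linear trend, the slope test would run at about 15–23%.

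For CAPS-5 and PEth, uneven spacing is a minor matter. The single-variance assumption is the more relevant one there, and it can move standard errors either way.

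Constant variance is also doubtful for alcohol on the plan's own terms. Baseline and follow-up TLFB cover the past 90 days, while the TLFB before each session has no stated window. If that window is shorter, weekly grams averaged over different periods would be expected to have different variances.

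This should be changed before the analysis. The documents do not show that any particular standard error will be wrong. They show a covariance that does not fit the schedule on its ordinary reading, with no safeguard.

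**What to change.** **Alcohol and PCL-C.** Index the serial correlation by actual weeks since randomisation: continuous-time autoregressive plus random intercept, with a measurement-error term and variances allowed to differ by visit. Alternatively, report robust standard errors. State whether time is categorical, and state the TLFB window used at each session.

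**CAPS-5 and PEth.** Use an unstructured covariance over the five visits and drop the random intercept, which it absorbs. Keep REML and the Satterthwaite approximation.

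**Fallback and sensitivity.** Name one fallback in advance for non-convergence, for example the week-based structure with visit-specific variances for the five-visit outcomes. Because the SAP already refers to participant data, date and justify the change and report the present AR(1) model as a sensitivity analysis.

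**Cost.** A sentence or two per outcome and a documented SAP amendment. The five-visit models go from 3 covariance parameters (intercept variance, residual variance, correlation) to 5 × 6/2 = 15, that is 12 more, which up to 150 participants should support.
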